### Outcome measures

#### Primary outcome measure

The primary endpoint of the study is the frequency of incisional hernias 1 year postoperatively, as assessed by ultrasound examination.

An incisional hernia is defined as an ‘abdominal wall gap with or without bulging in the area of a postoperative scar perceptible or palpable by clinical examination or imaging’ according to the European Hernia Society. Incisional hernias will be classified according to their localization and size.

#### Secondary outcome measures

The length of hospital stay, cost, and quality of life, and the frequency of short term and long term complications will be compared between the short stitch and the long stitch group.

The length of hospital stay is defined as the time period from the day of surgery until the day of discharge.

The assessment of costs includes the material cost (suture), cost per operation minute (duration for abdominal wall closure), cost of hospital stay, and the cost saving per prevented incisional hernia.

To analyze quality of life, the EQ-5D-5 L questionnaire will be used and documented by the patient preoperatively, and after 30 days, 1 year, 3 years, and 5 years postoperatively. The EQ-5D-5 L is used in the German language version and a license has been obtained from the EuroQol Group by the sponsor. The EQ-5D is a standardized measure of health status developed by the EuroQol Group to provide a simple, generic measure of health for clinical and economic appraisal. The questionnaire is designed for self-completion by respondents and takes only a few minutes to complete. Instructions to respondents are included in the questionnaire. The EQ-5D-5 L consists of two pages a descriptive system and the EQ Visual Analogue Scale (EQ-VAS). The descriptive system comprises five dimensions (mobility, self-care, usual activities, pain or discomfort, anxiety or depression). Each dimension has five levels: no problem, slight problems, moderate problems, severe problems, and extreme problems. The EQ-VAS records the respondent’s self-rated health on a 20 cm vertical visual analogue scale with endpoints labeled ‘the best health you can imagine’ and ‘the worst health you can imagine’.

Short term complications include the frequency of burst abdomen and the reoperation rate due to burst abdomen until day of discharge. Wound infections occurring until the day of discharge and within 30 days after surgery will be recorded as short term complications. Wound infections are defined according to the US Centers for Disease Control and Prevention (CDC). Furthermore, wound healing complications, such as seroma, necrosis, and fistula, reported until 30 days postoperatively will be counted as short term complications.

Long term complications include the frequency of incisional hernias after 3 and 5 years after surgery, ad detected by ultrasound examination. Furthermore, wound infections according to CDC classification 1 year postoperatively and wound healing complications occurring within 1 year after surgery will be investigated.

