## Methods

### Study design

The Effect of Suture Technique on the Occurrence of Incisional Hernia (ESTOIH) study is a prospective, international, multicenter, double-blinded, randomized controlled trial, aimed at evaluating the efficacy of the short stitch suture technique using an elastic, extra-long term absorbable monofilament suture (MonoMax®) after primary median laparotomy, in comparison with the long stitch suture technique.

In total, 468 patients will be enrolled in seven centers located in Germany and Austria. Patients will be randomly allocated to receive either the short or the long stitch suture technique for abdominal wall closure in a 1:1 ratio. The surgical procedure used to close the abdomen will be standardized in both suture technique groups and the participating centers will be trained in the different suture techniques.

After the operative procedure, the investigator will examine the patients on the second day after surgery, on the day of discharge, and at 30 days ±10 days, 1 year ±1 month, 3 years ±3 months and 5 years ±3 months postoperatively. Patients and observers performing the follow-up visits will be unaware of the suture technique (double-blinded) used. The study will last 5 years for each patient (Figures 1 and 2).

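### Burst abdomen is counted only until discharge: a later burst is named in no endpoint, and each patient's observation time equals length of stay

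*Protocol article*

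**What the plan says.** All of the relevant definitions are in the protocol article. Secondary outcome measures sets the window for this event: "Short term complications include the frequency of burst abdomen and the reoperation rate due to burst abdomen until day of discharge".

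The same paragraph treats the neighbouring wound events differently. For infection: "Wound infections occurring until the day of discharge and within 30 days after surgery will be recorded as short term complications". For healing: "wound healing complications, such as seroma, necrosis, and fistula, reported until 30 days postoperatively will be counted as short term complications". The list of long-term complications then carries these two further: "wound infections according to CDC classification 1 year postoperatively and wound healing complications occurring within 1 year after surgery will be investigated". It does not name burst abdomen.

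Discharge is also the end of another outcome. The section states that "The length of hospital stay, cost, and quality of life, and the frequency of short term and long term complications will be compared" between the two groups, and that "The length of hospital stay is defined as the time period from the day of surgery until the day of discharge".

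Study design schedules examinations on the second day after surgery, "on the day of discharge, and at 30 days ±10 days", and then at 1, 3 and 5 years. A contact near day 30 therefore already exists.

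Secondary endpoints gives the two-sided chi-square test for proportions and Kaplan-Meier for other rates, with event dates. It does not say which applies to burst abdomen. Statistical analysis makes all secondary endpoints exploratory.

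**The concern.** Burst abdomen is a direct failure of the closure that this trial compares. A window that ends at discharge has two consequences.

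First, a burst that happens at home is outside the definition, even though the patient is seen again at about 30 days and infections and healing problems are counted up to that time.

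Second, the window has no fixed length. It starts at surgery and stops at discharge, so it is the patient's length of stay. That is determined after randomisation and is compared as an outcome in its own right. If one technique led to earlier discharge, that arm would be watched for less time and would show fewer bursts at the same true risk. A chi-square comparison of proportions makes no allowance for this.

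At stake is the reading of the short-term comparison of burst abdomen and of reoperation for it. The confirmatory hernia comparison is not at stake.

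**Working it through.** **Windows side by side**

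| Event | Short-term window | Named later? |
|---|---|---|
| Burst abdomen, and reoperation for it | Surgery to discharge | No |
| Wound infection | To discharge and within 30 days | Yes, at 1 year |
| Wound healing complications | To 30 days | Yes, within 1 year |
| Length of stay (compared outcome) | Surgery to discharge | Not applicable |

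The first and last rows have the same start and the same end, so time at risk for burst abdomen and length of stay are one quantity.

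**Inputs.** The article gives no burst abdomen rate, no onset distribution and no length of stay, so it contains no figure on this point to reproduce. The sample size (212 per group) rests on the hernia rates of 19% and 9.5% and is not touched. What follows is an illustration under assumptions:

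- the true 30-day risk is the same in both arms;
- onset is exponential with mean m = 5, 8 or 10 days before truncation at day 30;
- all patients in an arm are discharged on the same day t.

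**Formula.** The share of 30-day events that falls on or before day t is

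F(t) = (1 − exp(−t/m)) / (1 − exp(−30/m)).

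The share missed is 1 − F(t). With equal true risk, the apparent risk ratio for an arm discharged at day b against an arm discharged at day a is F(b)/F(a).

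**Example, m = 10.** F(10) = (1 − exp(−1)) / (1 − exp(−3)) = 0.632/0.950 = 0.665, so 33.5% of events are missed. F(8) = (1 − exp(−0.8)) / (1 − exp(−3)) = 0.551/0.950 = 0.580. The ratio of the unrounded values is 0.871.

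| m (days) | F(10) | Missed, discharge day 10 | F(8) | Apparent risk ratio, day 8 v day 10 | Apparent risk ratio, day 7 v day 14 |
|---|---|---|---|---|---|
| 5 | 0.867 | 13.3% | 0.800 | 0.923 | 0.802 |
| 8 | 0.731 | 26.9% | 0.647 | 0.886 | 0.706 |
| 10 | 0.665 | 33.5% | 0.580 | 0.871 | 0.668 |

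With the same discharge day in both arms, F(b)/F(a) = 1. Events are lost, but the ratio is not distorted.

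**The case against.** The strongest reply is that little escapes and little depends on it.

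- **Other endpoints catch part of it.** A reader might infer that closure failures after discharge appear in no endpoint. The article does not support that. Primary outcome measure counts any abdominal wall gap in the scar area at 1 year, and hernias are sought again at 3 and 5 years, so a persisting failure is counted. The list of healing complications is open-ended, and Safety plans listings and tables with no cut-off at discharge. A late dehiscence could enter either. This stands, and it narrows the point to burst abdomen as a named event. Neither route names burst abdomen or ensures that the arms are compared on it over a fixed period.
- **Kaplan-Meier handles unequal follow-up.** This stands only in part. The method is not assigned to burst abdomen. It cannot recover events that the definition excludes, and it needs censoring to be uninformative. Discharge is unlikely to be so, since patients tend to go home when they are doing well.
- **The wording is ambiguous.** The limit at discharge could be read as applying only to the reoperation rate. Burst abdomen would then have no stated window, and the sentence would still need correction.
- **The article condenses a fuller protocol.** It does, but this is a definition that it states. The same paragraph distinguishes discharge from 30 days and gives burst abdomen only the former.
- **No difference in stay is shown.** This stands. Nothing in the article suggests that stay will differ between arms, and patients and outcome observers are blinded.
- **The endpoint is secondary and exploratory.** This stands and limits the weight of the point.

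**Conclusion.** The point holds in a limited form. The burst abdomen window ends at discharge, not at a fixed time. A burst after discharge is named in no endpoint, and one that is re-closed without a gap at 1 year may escape all of the named endpoints. Time at risk is tied to a compared outcome.

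The size cannot be established from the article. Under the assumed onset pattern, discharge at day 10 misses 13.3% to 33.5% of 30-day events. A two-day difference in stay (day 8 against day 10) gives an apparent risk ratio of 0.92 to 0.87, and day 7 against day 14 gives 0.80 to 0.67. These ratios need a difference in stay between arms. Without one, the loss is of events only.

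Three stronger readings are not supported:

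- *The burst comparison will be biased.* The article gives no sign that stay differs by arm.
- *The hernia endpoint rewards a re-closed burst.* Under Primary endpoint, the hernia rate is a cumulative Kaplan-Meier estimate using the date of first observation. The text does not settle whether a gap recorded before re-closure counts. The same question arises for a burst in hospital, so it does not come from the discharge window. A composite of burst and hernia would be a separate design choice.
- *The tolerance of the 30-day visit leaves a third of the window unobserved.* A visit at day 20 leaves 10 of 30 calendar days, but only for a patient seen on the earliest permitted day. That is not a share of events, and a later contact can complete the period.

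**What to change.** Define burst abdomen, and reoperation for it, over a fixed window from surgery to day 30 for every patient, with the event date. Collect both at the existing 30-day visit. For a patient seen before day 30, complete the status to day 30 at the next contact or from records. The count until discharge may stay as a descriptive figure.

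The cost is a wording change to an exploratory secondary endpoint and one case report form item. No visit or patient is added, and the primary analysis and sample size do not change. Trial status reports 55 of 468 patients randomised when the article was being completed, so 468 − 55 = 413 (88%) were still to come. Patients already past day 30 can be completed from records.

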### Sample size calculation

The ISSAAC study has shown a risk of 19% of developing an incisional hernia within one year using MonoMax® suture material and a long stitch technique for abdominal wall closure of a primary elective midline laparotomy [14]. The aim of this study is to demonstrate that the short stitch suture technique with MonoMax® will decrease the incisional hernia rate after 1 year by 50% compared with the long stitch technique (primary endpoint). Considering hernia rates of 19% and 9.5% in both groups, a total sample size of 424 patients (212 per group) will be necessary to detect this difference with a power of 80% and an alpha of 5%. Including a drop-out rate of 10%, a total of 468 patients will be randomized in the current study. Thus, each of the seven participating centers should recruit about 67 patients. To avoid center effects, a maximum of 200 patients may be recruited per center. Withdrawn patients will not be replaced.

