### Primary endpoint

The study hypothesis will be tested by a two-sided chi square test for independent proportions.

The hernia rate is calculated as a Kaplan-Meier estimate for the failure rate at the end of the observation period (1 year ± 1 month). The Kaplan-Meier estimate has the benefit of additionally taking into account the results of drop-out patients. For each hernia, the date of its first observation must be documented to provide a correct estimate. The date of hernia detected by ultrasound at a follow-up examination will be set to the examination date; this may lead to a slight over-estimation of the hernia rates in both groups.

Analyses will be performed according to the intention-to-treat principle. The consistency of the results will be tested by per-protocol analysis (sensitivity analysis).

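### With 468 randomised and the stated 10% drop-out, about 421 patients remain, slightly fewer than the 424 the protocol calls necessary

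*Protocol article*

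**What the plan says.** All the figures stand in the protocol article under Methods, Sample size calculation. The planning rates are given first: "Considering hernia rates of 19% and 9.5% in both groups". From these, with 80% power and a 5% alpha, the protocol concludes that "a total sample size of 424 patients (212 per group) will be necessary to detect this difference". It then allows for losses: "Including a drop-out rate of 10%, a total of 468 patients will be randomized in the current study". The same paragraph closes off one way of recovering lost patients: "Withdrawn patients will not be replaced".

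Two other sections supply what is needed to repeat the calculation. Study design sets 1:1 allocation. Primary endpoint (under Statistical analysis) names the test: "The study hypothesis will be tested by a two-sided chi square test for independent proportions". That section also says that the 1-year hernia rate is a Kaplan-Meier estimate, which makes some use of patients who drop out. The protocol does not state the formula by which 424 became 468.

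**The concern.** A drop-out rate is ordinarily a share of the patients randomised. To finish with a required number N after losing a fraction d, one randomises N/(1 − d). Multiplying N by (1 + d) gives too few, because the loss then applies to the enlarged total and not to N. The total of 468 looks like the result of multiplying.

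If so, the protocol's three figures (424 necessary, 10% lost, 468 randomised) cannot all hold. At stake is the accuracy of the sample size justification: 468 is the headline enrolment figure, also given in the Abstract and in Study design, and a reader will take it as securing the stated 80% power at 10% drop-out.

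**Working it through.** **Inputs**

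| Input | Value | Protocol section |
|---|---|---|
| Hernia rate, long stitch (p₁) | 0.19 | Sample size calculation |
| Hernia rate, short stitch (p₂) | 0.095 | Sample size calculation |
| Power, alpha | 80%, 5% | Sample size calculation |
| Test | two-sided chi-square | Primary endpoint |
| Allocation | 1:1 | Study design |
| Drop-out (d) | 0.10 | Sample size calculation |
| Randomised | 468 | Sample size calculation |

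**Step 1: reproduce 424.** The two-proportion formula with pooled variance under the null and no continuity correction is

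n per arm = [z₀.₉₇₅ √(2 p̄(1 − p̄)) + z₀.₈₀ √(p₁(1 − p₁) + p₂(1 − p₂))]² / (p₁ − p₂)²

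- p̄ = (0.19 + 0.095)/2 = 0.1425, so √(2 × 0.1425 × 0.8575) = 0.4944.
- √(0.19 × 0.81 + 0.095 × 0.905) = √0.239875 = 0.4898.
- n = (1.960 × 0.4944 + 0.8416 × 0.4898)² / 0.095² = 211.4, rounded up to 212 per arm and 424 in total.

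This matches the protocol exactly. The usual variants do not: unpooled variance gives 418 in total, a continuity correction 464, and a one-sided test 334.

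**Step 2: reproduce 468.**

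- Adding 10% per arm: 212 × 1.10 = 233.2, rounded up to 234; 2 × 234 = 468. This is an exact match.
- Dividing by 0.90 per arm: 212/0.90 = 235.6, rounded up to 236; 2 × 236 = 472. This does not match.

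That 10% was added is therefore an inference from the match. Step 3 does not depend on it.

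**Step 3: what 468 delivers.**

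- Remaining after 10% loss: 468 × 0.90 = 421.2, or 210.6 per arm. Shortfall: 424 − 421.2 = 2.8 patients.
- Largest drop-out that still leaves 424: 1 − 424/468 = 9.4%.
- Check on 472: 472 × 0.90 = 424.8, which is at least 424.

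**Step 4: effect on power.** From the same formula,

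power = Φ{[(p₁ − p₂)√n − 1.960 × 0.4944] / 0.4898}

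| Patients analysed | Per arm | Power |
|---|---|---|
| 424 | 212 | 80.1% |
| 421.2 | 210.6 | 79.9% |

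To two decimals these are 80.12% and 79.86%, a difference of about 0.3 percentage points.

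**The case against.** The best case for the protocol is that nothing of consequence fails.

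- **Power survives rounding.** 79.86% is 80% at the precision the protocol uses. The unrounded requirement is about 2 × 211.4 = 422.8, and against that the shortfall is under 2 patients. The uncertainty in the assumed 19%, the halving and the 10% is far larger. This stands, and it is why the point ranks as minor.
- **The sentence may mean 10% on top of 424.** The protocol does not define the base of the percentage, and on that loose reading 468 is consistent. But patients drop out from among those randomised, so this is not the usual meaning of a drop-out rate. If it was intended, the sentence should say so.
- **Drop-outs still contribute.** The Primary endpoint section plans an intention-to-treat analysis and a Kaplan-Meier rate that makes use of drop-outs, and the protocol nowhere says that the 424 must be fully observed. Part of this stands: some partial information is kept. It does not restore 424, however. The size was computed for a comparison of two proportions and then enlarged for drop-out, so the plan itself counts drop-outs as lost. After discharge there is only the 30-day visit before the 1-year visit, and a hernia found by ultrasound at follow-up takes the date of that examination. A patient lost before 1 year therefore usually adds little about the 1-year rate.

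**Conclusion.** The stated figures are inconsistent: 468 randomised with 10% drop-out and no replacement leaves about 421 patients, not 424. The gap is 4 patients at randomisation (472 against 468, or 0.8%), about 3 at analysis, and about 0.3 percentage points of power. It rests on reading the 10% as a share of those randomised and on treating drop-outs as not contributing to the 1-year comparison, as the protocol's own allowance does. It does not rest on how 468 was obtained. This is an arithmetic slip in a planning figure. The calculation of 424 is correct, and the trial is not underpowered in any practical sense because of it.

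**What to change.** Correct the one sentence on drop-out in Sample size calculation, in either of two ways:

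- state that 468 randomised patients allow for a drop-out of up to 9.4% while keeping 424; or
- keep the 10% assumption and state that 468 randomised patients then leave about 421, with 79.9% power.

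The second is preferable, since it leaves the planning assumption alone and avoids giving an assumed rate a precision it does not have. The cost is one sentence and a marginally less favourable stated figure. Enrolment, centre targets and the analysis stay as they are. Raising the total to 472 would also reconcile the figures, but the gain in power does not call for it.

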### Statistical analysis

A planned analysis will be performed after all patients have completed their 1 year follow-up (primary endpoint). All data available until 1 year follow-up will be analyzed. Additional analyses will be conducted after completion of the 3 and 5 year follow-ups. It is intended to publish the 1 year result as well as the 3 and 5 year results in a peer-reviewed journal.

The statistical analysis of the primary endpoint has a confirmative character, whereas the secondary endpoints will be analyzed exploratively.

The description of the patient cohort with respect to demographic data and the baseline values of investigated parameters will take place as a whole as well as grouped by treatment group.

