## Abstract

**Background:**

Based on a recent meta-analysis, a continuous suture technique with a suture to wound length ratio of at least 4:1, using a slowly absorbable monofilament suture material, is recommended for primary median laparotomy closure. Incisional hernia, which develops in 9 to 20% of patients, remains the major complication of abdominal wall closure. Current clinical data indicate that the incidence of incisional hernias increases by 60% between the first and the third year after median laparotomy, implicating that a follow-up period of 1 year postoperatively is too short with regard to this common complication. Trauma to the abdominal wall can be reduced by improvements in suture technique as well as suture material. Several factors, such as stitch length, suture tension, elasticity, and tensile strength of the suture material are discussed and currently under investigation. A Swedish randomized controlled trial showed a significant reduction in the incisional hernia rate by shortening the stitch length. However, a non-elastic thread was used and follow-up ended after 12 months. Therefore, we designed a multicenter, international, double-blinded, randomized trial to analyze the influence of stitch length, using an elastic, extra-long term absorbable monofilament suture, on the long term clinical outcome of abdominal wall closure.

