**Discussion:**

This study will provide further evidence on whether a short stitch suture technique in combination with an elastic, extra-long term absorbable monofilament suture can prevent incisional hernias in the long term, compared with the long stitch suture technique.

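### The long-term hernia difference that motivates the trial has only exploratory status; naming 3-year incidence as a gated key secondary endpoint would allow an error-controlled claim at no alpha cost to the primary test

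*Protocol article*

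**What the plan says.** **Rationale.** The Background part of the abstract says that "a follow-up period of 1 year postoperatively is too short with regard to this common complication", because incidence rises by 60% between the first and third year. It notes that the earlier Swedish trial stopped at 12 months and used a non-elastic thread, and presents the new trial as a response. The abstract and the main Background section both give the aim as long-term clinical outcome. The Discussion part of the abstract says the study will add evidence on whether the short stitch technique with this suture "can prevent incisional hernias in the long term". The main Discussion repeats the 60% rise as something to be taken into account.

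**Formal plan.** The primary endpoint is hernia frequency at 1 year by ultrasound. The sample size section sets the aim as a 50% reduction at 1 year: "Considering hernia rates of 19% and 9.5% in both groups, a total sample size of 424 patients (212 per group) will be necessary". The Primary endpoint section adds: "The study hypothesis will be tested by a two-sided chi square test for independent proportions".

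**Later time points.** Under Secondary outcome measures: "Long term complications include the frequency of incisional hernias after 3 and 5 years after surgery", also by ultrasound. Analyses after the 3- and 5-year visits are planned, with publication. Their status is fixed under Statistical analysis: "The statistical analysis of the primary endpoint has a confirmative character, whereas the secondary endpoints will be analyzed exploratively".

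**The concern.** The result that answers the question in the rationale has the same inferential rank as cost and length of stay. If the 1-year test succeeds, the trial can make a confirmatory claim at 12 months, the horizon its own rationale calls too short. Whatever the 3-year comparison shows, it remains exploratory.

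This is not a detail that a condensed article leaves to a fuller document. The article states the status of all secondary endpoints. The visits, the ultrasound examinations, the 3-year analysis and its publication are already planned. What is missing is a place for the 3-year comparison in a testing order.

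**Working it through.** **1. The plan's own figure.** Inputs from the Sample size calculation and Primary endpoint sections: 19% and 9.5%, two-sided 5%, 80% power, chi-square test. With pooled variance and no continuity correction,

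n = [1.960·√(2p̄(1−p̄)) + 0.8416·√(p₁(1−p₁)+p₂(1−p₂))]² / (p₁−p₂)².

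Here p̄ = 0.1425, so n = [1.960·√0.24439 + 0.8416·√0.239875]² / 0.095² = (0.969 + 0.412)² / 0.009025 = 211.4. This rounds up to 212 per group, 424 in total, as stated. The 468 randomised are 234 per arm.

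**2. Rates at 3 years (assumption).** Read the 60% as a relative rise, equal in both arms:
- long stitch: 19% × 1.6 = 30.4%
- short stitch: 9.5% × 1.6 = 15.2%, so the 50% reduction persists.

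As a weaker effect, take the relative risk of the other trial quoted in the Discussion, 14% against 23%: 14/23 = 0.61. This gives 19% against 11.6% at 1 year and 30.4% against 18.5% at 3 years.

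**3. Power at 3 years taken alone.** The article gives no loss figure for 3 years; its 10% belongs to the 1-year calculation. A range of 10% to 40% is therefore shown.

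Power = Φ{[|p₁−p₂|·√n − 1.960·√(2p̄(1−p̄))] / √(p₁(1−p₁)+p₂(1−p₂))}.

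Example at 10% loss, n = 210, p̄ = 0.228: (0.152·14.491 − 1.960·0.5933) / 0.5835 = (2.203 − 1.163) / 0.5835 = 1.78, so power is 96%.

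| Loss at 3 years | Relative risk 0.50 | Relative risk 14/23 |
|---|---|---|
| 10% | 96% | 81% |
| 20% | 94% | 77% |
| 30% | 91% | 71% |
| 40% | 86% | 64% |

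If the absolute difference stays at 9.5 points instead (30.4% against 20.9%), power at 10% loss is about 61%.

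**4. Chance of passing both tests in sequence.** A 3-year test that opens only after a significant 1-year test cannot succeed more often than the 1-year test does. At 10% loss, 1-year power is about 80% for 19% against 9.5%, and about 56% for 19% against 11.6%. The joint chance was simulated in nested patients: a hernia present at 1 year still counts at 3 years, and new hernias are added to reach the 3-year rates.

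| Scenario | 3-year test alone (10% to 40% loss) | Both tests in sequence |
|---|---|---|
| Relative risk 0.50 | 96% to 86% | about 80% to 74% |
| Relative risk 14/23 | 81% to 64% | about 54% to 46% |

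With a persistent 50% reduction, most of the uncertainty lies in the 1-year test, and the 3-year step loses little.

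**5. Cost of the alternative.** Splitting alpha equally, 2.5% at each time point, would lower 1-year power from about 80% to about 71% with 210 per group. A fixed sequence leaves 1-year power unchanged.

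**The case against.** The strongest reply is that the plan is consistent about its formal aim. The sample size section places it at 1 year, the primary endpoint and test agree, and the abstract promises only further evidence on the long term. An exploratory randomised comparison can supply that. One confirmatory endpoint with exploratory secondary endpoints is a conventional choice, disclosed in advance, and it inflates no error rate. The criticism of the earlier trial concerned its thread and its length of follow-up, and this trial changes both. All of this stands. A reader might infer that the plan contradicts itself or that the primary analysis is unsound; the documents support neither.

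A reader might also take the 3-year power of 96% or 81% as the yield of the proposed change. It is not, because the 1-year test gates it; the joint figures are the relevant ones.

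A third tempting reading is that a 3-year test would separate a gain that lasts from one that fades. It would not. A significant result shows a difference at 3 years, and a non-significant one does not show that the effect has gone. Durability is better judged from estimates with confidence intervals, for which the plan already provides.

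Finally, eligibility requires expected survival only beyond 1 year, so deaths before year 3 may matter. This does not defeat the proposal, but it adds work to it.

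What remains is that estimation alone carries no error-controlled claim at the horizon the rationale calls necessary, and such a claim can be had cheaply.

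**Conclusion.** The point holds as a worthwhile improvement to the inferential status of the 3-year result. The trial can estimate the long-term difference but cannot claim it with type I error control, and the cause is the assigned exploratory status. If the planned relative effect persists, the sample size is not the obstacle: about 119 per group would give 80% power at 30.4% against 15.2%, and 40% loss would still leave 140.

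The chance of a confirmed 3-year difference is about 80% to 74% with a persistent halving of risk and about 54% to 46% at a relative risk of 14/23. These figures assume that the 60% rise is relative and equal in both arms, that 1-year loss is 10%, and that 3-year loss is between 10% and 40%. A constant absolute difference would be less favourable: about 61% at 10% loss even before gating. Low power at 3 years would not harm the 1-year claim.

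**What to change.** Keep the 1-year primary endpoint and its test. Before the 1-year analysis is unblinded, state that:
- 3-year hernia incidence is a key secondary endpoint, tested at two-sided 5% only if the 1-year test is significant;
- 5-year incidence may follow third, on the same condition;
- all other secondary endpoints stay exploratory;
- deaths and losses before year 3 are handled by a rule fixed in advance.

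The timing matters because the 1-year result is to be analysed and published first. If the sponsor prefers not to add the sequence, confirmatory conclusions should be limited to 12 months, and the 3- and 5-year results reported as estimates with confidence intervals.

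Cost: a short amendment or analysis-plan text, including the rule for deaths and losses. It needs no alpha from the primary test, no extra visits and no extra patients. The downside is that a confirmatory 3-year claim depends on success at 1 year.
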